#### 3.13 Data management and analysis

All baseline, surveillance and laboratory data will be collected on forms designed for the trial. Field and laboratory staff will be trained to follow the procedures set out in a series of Standard Operating Procedures (SOPs). Key data will be double entered and inconsistencies checked; range checks will be used for standard variables. Primary analyses will be performed on an intention to treat (ITT) basis. Any child who receives a first dose of drug will be included in the ITT analysis. Children who are randomised but who do not receive any mediation will not be included in this analysis.

*3.14 Sample s-size calculations*

Drugs for IPT need to be acceptable and have low frequency of adverse events. If the frequency of adverse events is 20% in the SP/AQ group, a trial with 286 children per arm has 90% power to detect a halving in the frequency of adverse events, using a significance level of 0.05, or a reduction to 9% or less if a significance of 0.025 is used (to preserve an overall type 1 error rate of 5% for the primary endpoint when there are 2 comparisons, each alternative drug group with SP/AQ). If the frequency of adverse events is 15%, a reduction to 5% or less can be detected with the same power, and if the frequency is 10% a reduction to 2% or less can be detected. Based on experience from several studies the drop-out rate is not expected to exceed 15% and is likely to be less. Allowing for 15% drop out, a sample size of 286*3/(1-0.15)=1009 is needed.

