It is not certain whether IPTc could be effectively delivered through the infrastructure of the Reproductive and Child Health (RCH) service given the ever increasing workload of the RCH clinics. With support from the Gates Malaria Partnership, a study to compare two strategies for the delivery of intermittent preventive treatment in children was undertaken in 2006 in 14000 children in Upper River Division of The Gambia where malaria transmission is seasonal. Twenty-six RCH trekking clinics in Upper River Division were randomly allocated to receive IPT from the RCH trekking team or from a village health worker. Treatment with a single dose of sulfadoxine /pyrimethamine (SP) plus three doses of amodiaquine was given to all study subjects at monthly intervals on three occasions during the months of September, October and November. Preliminary analysis of the results showed that the treatment was very effective as only 4% (45/1133) of the children seen at the end of year cross-sectional survey were parasitaemic. Compliance was initially high but decreased progressively with increase in the number of doses taken by the study subjects. 81%, 74% and 67% of study subjects in the VHW arm received IPT during September, October and November respectively. In the RCH arm, 69%, 51% and 48% received IPT during September, October, and November respectively. Tolerability was assessed in a subset of 1100 children and the results showed that about 13.5% of children developed mild to moderate vomiting but there was no control group for comparison. Mild to moderate malaise was present in about 10% of the study subjects. Severe adverse event was rare. However, these adverse events had a negative impact on compliance because of the perception among the study population that the trial medication was associated with a significant number of adverse events. Thus, it is important to investigate if other drug combinations might be equally effective in preventing malaria but more effective in preventing adverse events. Thus, we now propose to compare the safety, efficacy and tolerability of three potential drugs combinations for IPTc. The drugs combinations that we have selected for comparison are amodiaquine plus sulfadoxine-pyrimethamine (the combination used in the previous study), sulfadoxine-pyrimethamine plus piperaquine (another long acting drug) and Artekin TM (dihydoartemsinin plus piperaquine).

*1.2.4 Potential drugs for use in IPT*

Amodiaquine

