***Withdrawal Criteria***

Study subjects may be withdrawn from the study for any one of the following reasons.

1. Withdrawal of parental / legal guardian’s consent.
2. Serious adverse event attributable to the study drug.
3. Loss to follow-up.

Children who develop adverse events attributable to study drugs should not receive further doses but should be followed-up to monitor safety up until the resolution of the adverse reaction.

*3.6 Randomisation*

Open-label, individual randomisation is proposed and will be done approximately three weeks before the first dose of IPTc administration planned for early September 2007. Study subjects will be individually randomised into either the AQ plus SP, PQP plus SP or ArtekinTM treatment groups in a 1:1:1 fashion. An independent statistician will generate the randomizing subject study number (SSN) that associates each SSN either to AQ plus SP, PQP plus SP or Artekin TM treatment groups and study subjects will be given treatment according to their randomisation group. A photo ID card will be given to all participants to facilitate identification at every contact, at home or in the health centres.

*3.7 Drug distribution at the health centres*

Study subjects and their parents will be informed about the date of treatment approximately one week before any intervention. Treatment will be given during the months of September, October and November. Drugs will be given at the nearest health centre by a designated member of staff. Tablets will be crushed, mixed with honey or suspended in water and given on a spoon. Staff who administer drugs at the health centre will play no further part in the trial. All participants will be kept under observation for 30 minutes after drugs are taken. In case of vomiting, the drug will be re-administrated. At the time of each monthly drug administration, a brief clinical assessment will be carried out. Children who are febrile will be screened for malaria using a rapid antigen test. Children found to have malaria will be treated with Lumefantrine-artemether (CoartemTM, Norvatis Pharma., Basel Switzerland).

*3.8 Treatment*

SP (tablets containing 500 mg sulfadoxine/ 25 mg pyrimethamine) will be given at an approximate dose of 1.25 mg pyrimethamine/25 mg sulfadoxine per kg stat.

Amodiaquine (200 mg base tablets) will be given at an approximate dose of 25 mg/kg over 3 days ( 10mg/kg D1, 10mg/kg D2 and 5mg/g D3).

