# *3.11 End of malaria transmission season cross-sectional survey*

Children enrolled in the study will be seen at the OPD clinic at the end of malaria transmission season for examination by a study physician and a finger-prick blood sample will be obtained for preparation of a thick blood smear and determination of haemoglobin concentration. A standardized questionnaire will be administered to the parents/guardians of the study subject, to collect information regarding illness that had occurred since the last visit, symptoms experienced, use of healthcare facilities and use of medicines. Information on the use of bed nets will be collected again at this visit.

*3.12 Study end-points:*

*3.12.1 Primary end points*

*Safety endpoint*

- Incidence of any adverse events during the observation period.

*Secondary end points*

- Mean Hb (g/dl) at the end of malaria transmission.
- Prevalence of malaria parasitaemia at the end of the malaria transmission season.
- Number of OPD attendances with malaria that meet the case definitions as indicated below during the surveillance period.

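### The analysis called intention to treat leaves out never-dosed children, although allocation is open-label and made about three weeks before the first dose

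*Protocol*

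**What the plan says.** Section 3.13 puts the primary analyses on an intention-to-treat basis and then defines the set by dosing. A child enters on receiving a first dose, and "Children who are randomised but who do not receive any mediation will not be included in this analysis".

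Section 3.6 fixes the timing: "Open-label, individual randomisation is proposed and will be done approximately three weeks before the first dose of IPTc administration". The three arms are allocated "in a 1:1:1 fashion". Section 3.7 adds two facts about what follows allocation: "Study subjects and their parents will be informed about the date of treatment approximately one week before any intervention", and "Drugs will be given at the nearest health centre by a designated member of staff".

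The only masking stated is in 3.9.1, where the field workers who complete the side-effects questionnaire do not know the child's arm. Section 3.6 has an independent statistician generate the allocation, and 3.7 keeps dosing staff out of the rest of the trial. Neither section says when families or dosing staff learn the arm.

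Two sources of outcome data are not tied to dosing. For the survey in 3.11, "Children enrolled in the study will be seen at the OPD clinic at the end of malaria transmission season". Passive surveillance in 3.10 covers children in the trial.

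**The concern.** Dropping never-dosed children does little harm when the arm is unknown until dosing, because the decision to attend cannot then depend on it. Here the arm exists, unmasked, for about three weeks before a family has to bring the child to a health centre. A family that learns the arm and stays away removes its child from the analysis.

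The protocol supplies a reason why this could happen unequally. Section 1.2.3 says that perceived adverse events of the 2006 regimen, SP plus AQ, reduced compliance. The same regimen is now the comparator arm in the same division. Families reluctant to attend may also be readier to report symptoms, which bears on the primary endpoint, or may differ in malaria risk and care-seeking, which bears on the secondary ones. The intention-to-treat label would hide this, since a reader would assume that every randomised child had been kept.

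**Working it through.** **1. The plan's own figure.** Inputs from 3.14: 20% v 10%, significance level 0.05 (taken as two-sided), power 90%.

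- n = [1.960·√(2·0.15·0.85) + 1.282·√(0.20·0.80 + 0.10·0.90)]² / 0.10² = 265.9 per arm.
- With continuity correction: (265.9/4)·[1 + √(1 + 4/(265.9·0.10))]² = 285.5, so 286. This matches the protocol.
- 286·3/0.85 = 1009.4. The protocol's 1009 is confirmed and gives 1009/3 = 336.3 randomised per arm.

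The sample-size calculation is therefore not at fault.

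**2. Room for non-starters.** The 15% allowance is 1009 − 858 = 151 children in all, and it must cover every kind of loss.

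The protocol does not estimate the never-dosed share. The nearest figures are the 2006 uptakes in 1.2.3: 81% in the first round with village health workers, and, for the clinic teams, "In the RCH arm, 69%, 51% and 48% received IPT during September, October, and November respectively". First-round non-receipt was thus 19% and 31%. These figures exceed the share never dosed in 2006, because a child who missed September could be dosed in October or November. They are used here only as an upper bound, with no further loss added.

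- 336.3 × 0.81 = 272 per arm
- 336.3 × 0.69 = 232 per arm

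Power for 20% v 10%, two-sided 0.05:

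| Analysed per arm | Continuity-corrected | Uncorrected |
|---|---|---|
| 286 | 0.901 | 0.920 |
| 272 | 0.884 | 0.906 |
| 232 | 0.825 | 0.857 |

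**3. How selection could distort the comparison.** Every input here is assumed, except the 0.025 level, which is the protocol's level for each of two comparisons. Suppose the drugs do not differ and that 20% of each full arm, about 336 children, would report an adverse event if all were dosed. Let 15% of the SP plus AQ arm and 5% of another arm never start. Let non-starters have r times the risk of starters. The rate among starters is then 0.20/(1 − d + d·r), where d is the never-dosed share.

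| r | SP plus AQ starters | Other arm starters | Type I error |
|---|---|---|---|
| 1 | 20.0% | 20.0% | 0.025 |
| 1.5 | 18.6% | 19.5% | 0.031 |
| 2 | 17.4% | 19.0% | 0.046 |
| 3 | 15.4% | 18.2% | 0.093 |

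If the never-dosed shares are equal in the two arms, the error stays at 0.025 whatever r is. Both conditions are needed: unequal non-starting, and a link between non-starting and risk.

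**The case against.** **The dosed set suits the primary endpoint.** Adverse-event visits are timed from drug administration (3.9.1), so never-dosed children may have no such data. This stands. For adverse events, what remains wrong is the label and the early open allocation.

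**The exclusion is written for the primary analyses.** Section 3.13 sets no population for haemoglobin, parasitaemia or clinical malaria, and an analysis plan not seen here may do so. This also stands: a reader might infer that the protocol excludes never-dosed children from the efficacy outcomes, but the text does not say so. It is still the only analysis set the protocol defines, so the efficacy set should be stated.

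**Families may not learn the arm early.** Section 3.7 says only that they are told the treatment date. Early knowledge is inferred from open-label allocation with no stated concealment, so the mechanism is possible but not documented.

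**The 2006 figures transfer poorly.** They come from a study of 14000 children that compared two delivery routes. This trial enrols individually consented volunteers who must be available throughout and who are given photo cards and advance notice. A reader might take 19-31% as the share that will be lost, but the documents do not support that. Nor is the gap between 81% and 69% evidence of drug avoidance, since both groups were offered the same regimen.

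**Other safeguards exist.** A reader might conclude that, once intention to treat fails, nothing protects the comparison. That is not so: questionnaire workers are blinded, an independent statistician generates the allocation, and dosing staff take no further part. None of these, however, governs who attends for the first dose.

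**Conclusion.** The point holds as a risk of bias. The set called intention to treat is an at-least-one-dose set, and with open allocation about three weeks ahead, entry to it can depend on the arm. The compliance history of SP plus AQ makes unequal non-starting plausible. The documents do not show that it will occur, or that non-starters would differ in risk.

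Under the assumed inputs above, type I error for one comparison rises from 0.025 to between 0.031 and 0.093, and it does not rise at all if either condition fails. The loss of power is secondary: at the borrowed upper bound, 272 to 232 children per arm would remain, with about 88-83% power (continuity-corrected) against the planned 90%. The true loss is likely to be smaller. This should be fixed, but it does not make the trial uninterpretable.

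**What to change.** 1. **Section 3.6.** Keep each child's allocation concealed, for example in sealed slips, and release it in study-number order only when the child attends for the first dose. Randomised and dosed children then nearly coincide. This is the step that protects the adverse-event comparison, because no later analysis can recover adverse-event data that were never collected. It has to be in place before allocation begins.
2. **Section 3.13, efficacy.** State that haemoglobin, parasitaemia and clinical malaria are analysed in all randomised children as allocated, where outcomes exist. The survey (3.11) and passive surveillance (3.10) do not depend on dosing.
3. **Section 3.13, safety.** Rename the at-least-one-dose set the safety (or modified intention-to-treat) population, use it for adverse events, and report the number of never-dosed children by arm with reasons.

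The cost is allocation slips at the dosing sites and a few sentences of protocol text. Any children who remain never dosed will slightly dilute the efficacy contrast.

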# *3.15 Ethical considerations*

The findings from this study could influence the choice of drug combination for IPTc in areas of seasonal transmission. Study children will benefit from the intensive follow-up during the study period. In addition, all malaria cases detected will be treated with an effective antimalarial. This study will not interfere with or limit access of study participants to the malaria prevention programme provided by the department of state for health. All of the drug combinations to be used in the study, amodiaquine plus SP, piperaquine plus SP and ArtekinTMm have been used extensively to treat or prevent malaria in young children and their safety profiles are well known.

*3.16 Oversight for the study*

A DSMB and Local safety monitor will provide oversight for the study

### Role of DSMB

The main role of the DSMB is to review and analyze clinical safety data collected during the trial and to assess unexpected or serious adverse events (SAEs).

The DSMC must be informed by the investigator of:

- serious and/or grade 3 adverse experiences occurring during the study (transmitted through the Local Safety Monitor)
- new information that may affect adversely the safety of the subjects or the conduct of the study.

###

### Role of Local Safety Monitor

The overall role of the Local Safety Monitor, who will be an experienced clinician, will be to support the clinical investigators and to act as a link between the investigators and the DSMB. All grade 3 adverse events probably or suspected to be related to trial medication and all serious adverse events will be reported to him in his capacity as a liaison to the DSMB. His involvement will be particularly important when decisions have to be made quickly.

